#### Activation: behavioral activation for depression scale [63]

The BADS is a 25-item self-report scale that intends to measure patients’ avoidance behavior and activity level during the past week. The scale includes four subscales: Activation, Avoidance/Rumination, Work- School and Social Impairment. Items are rated on a 7-point scale. Validity and reliability showed to be adequate [63].

#### Therapist adherence: collaborative study psychotherapy rating scale [64]

In order to measure therapists adherence to the treatment condition, independent raters will review a random selection of sessions by rating 76 items on a seven-point scale from the following subscales: Cognitive Behavioral Therapy (e.g. cognitive rationale, assessing cognitive processes, evaluating and changing beliefs, behavioral focus, homework and collaborative structure alternative cognitive strategies and operant approaches), Interpersonal Therapy (e.g. interpersonal rationale, focus on feelings, assessing interpersonal relationships and tendencies, assisting changes in interpersonal functioning, role transitions, interpersonal disputes, interpersonal deficits and interpersonal therapy scale ), Facilitative Conditions and Explicit Directiveness. Items regarding medication use and clinical management were omitted. High internal consistency and inter-rater reliability was reported [64].

#### Emotion Regulation: Action Control Scale 24 (ACS-24) [65, 66]

The ACS is a forced-choice self-report measure developed to assess differences in action-state orientation (the ability to initiate and maintain intentions). Two scales of the ACS will be used: action orientation subsequent to failure vs. preoccupation (AOF, 12 items, e.g. the ability to detach from thoughts about alternative goals or undesirable events that may interfere with progress on the task at hand.) and prospective and decision-related action orientation vs. hesitation (AOD, 12 items, e.g. the degree to which individuals have difficulty initiating intended goal-directed activities).

#### CT Skills: Competencies of Cognitive Therapy Scale-Self Report (CCTS-SR) [67, 68]

Two versions of this report will be used: a 29-item patient version and a 9-item therapist version. Both measures were designed to assess patients’ mastery of CT skills in the past two weeks. Patients rate the scale based on their skill use on a 1 (not at all) to 7 (completely) scale, while therapists evaluate a patient’s ability, independence, and frequency of use of behavioral activation, automatic thoughts, and core belief related CT strategies on a scale from 0 (none) to 6 (extensive). Psychometric properties seem promising [67].

#### Performance of CT Strategies (PCTS) [67]

Independent raters will assess the extent to which patients perform or intend to perform CT skills for a random selection of tapped sessions. The scale consist of 15 items that are rated on a 6-point Likert scale focusing on behavioral activation, automatic thought work, and schema or core belief work. Internal consistence has been shown to be sufficient [67].

#### Recall

Each session, therapists will rate the degree to which the patient seems to remember last session’s content on 10-point scale (0 = patient remembers nothing – 10 = patient remembers everything).

#### Maltreatment in childhood: Childhood Trauma Questionnaire-Short Form (CTQ-SF) [69]

To assess maltreatment in childhood, the Childhood Trauma Questionnaire-Short Form (CTQ-SF) is used. The CTQ-SF is a 28-item retrospective self-report questionnaire designed to assess five types of negative childhood experiences: (1) emotional neglect, (2) emotional abuse, (3) physical neglect, (4) physical abuse and (5) sexual abuse. In addition, tendencies to minimize or deny abuse experiences are measured. The truth of each statement is rated on a 5-point scale. Adequate reliability and validity has been shown [70, 71].

#### Automatic Thoughts: Cognition Checklist (CCL) [72]

The CCL investigates patients’ automatic thoughts and cognitions related to anxiety and depression. The scale consists of 26 items and is rated on a 5-point Likert scale. Internal consistency and validity was supported.

#### Executive functioning: n-back task [73]

During the n-back task patients are asked if a letter on the screen matches a letter previously (1-back, 2- back, 3-back) presented for 500 ms with an interval of 2000 ms. First, the patient will be asked to run a test trial, where he will get elaborate feedback about the incorrect responses (‘The previous letter was X, this indicated you had to press the button’). Second, the patient will complete a 1-back trial (two minutes) and a 2-back trial (two parts of 2.5 minutes). Only when the patient performs well on the 2-back (e.g. 2/3 correct responses; a correct response means a correct press or a correct no-press), he will be forwarded to the 3-back part of the task that will also take five minutes (two parts of 2.5 minute). Amount of targets in each condition will be 33 %. Feedback will be given after a correct response (marked by a green V) or a miss (marked by a black X). Working memory load increases as the task progresses from 1- back to 3-back and is suggested to require executive processes. The task will take a maximum of 12.5 minutes. Accuracy of responses (hits – false alarms) and reaction times will be measured. To prevent fatigue of the online assessments the patient will be asked to do the n-back task at another day than the other questionnaires.

#### Treatment preferences [74]

Patients preferences for either CT or IPT will be questioned before treatment by use of a 12-item questionnaire. A similar questionnaire was used in a previous study and adapted for use in the current trial.

### Instruments: biological measurements

Blood samples will be collected at baseline and after six months at the research sites. Blood samples will be collected using EDTA tubes (18 ml), serum tubes (6 ml) and PAX gene tubes (2 ml). EDTA 3 ml tubes will be sent to VUmc where DNA will be isolated followed by analysis of CpG islands adjacent to promoters I and IV. The serum tube, EDTA tubes (6 ml) and PAX tubes will be stored (e.g. in VUmc or hospitals near to the research locations) at −80 °C. After data collection (October 2016) all blood samples will be collected at VUmc. Use of medication and alcohol/drugs use in 24 hours before collecting the blood samples will be registered at baseline and after six months.

### Data-analyses

Data-analyses will include an intention-to-treat analysis and additional subgroup analyses.

### Data-analyses: primary outcome measures

Acute and long-term effects of the interventions (respectively 6 and 12 months) will be analyzed using mixed regression. This will enable us to use all outcome ratings and fit the growth curve of time, enter separate levels for study therapists and clinical sites, and also deal effectively with missing values. Time to recovery and relapse (episode of MDD after remission) and recurrence (episode of MDD after recovery) in the course of follow-up (12 and 24 months) will be analyzed with Cox regression. In addition, we will determine the proportion of patients that show reliable and clinically significant improvement on the outcome measures. Our calculations will be based on the method of Jacobson and Truax [75] which prescribes that Clinical Improvement (CI) is based on both Reliable Change (RC), the extent to which the pre-to-post-difference score is reliable; and on Clinical Significant change (CSC), the extent to which post-treatment scores are clinically meaningful [76]. Although the major question of this study focuses on the intensity of psychotherapy for depression, this study will additionally explore whether the effect of treatment intensity differs between IPT and CBT by testing an interaction between treatment conditions.

### Data-analyses: mechanisms of change

To identify mechanisms of change and the strength of the factors involved, both multilevel models and structural equation models (SEM, using path analysis in Mplus) will be used for mediation analyses. In a recent paper, for example, we used a latent difference score model to analyze mediation and temporality in the context of an RCT [77].

### Data-analyses: biological analyses

Levels of oxytocin, BDNF, methylation profile of the BDNF gene (e.g. CpG I and IV) and RNA marker profiles will be analyzed after finishing data collection. Pre- and post-treatment differences will be computed. The predictive value of the methylation profile of the BDNF gene (e.g. CpG I and IV) and RNA marker profiles on treatment outcome will be investigated.

### Data-analyses: cost-effectiveness

In order to evaluate cost-effectiveness a Cost Effectiveness Analysis (CEA) and Budget Impact Analysis (BIA) will be performed. Within the CEA the difference in societal costs (measured by the TiC-P at baseline and after 3, 6, 9 and 12 months) generated by patients in the two conditions (two sessions versus one session a week) will be related to the difference in clinical effects (measured with the BDI-II and quality- adjusted life-years (QALYS) based on the EQ-5D) over the course of twelve months. Missing cost and effect data will be treated using multiple imputation. Bootstrapping with 5000 replications will be used to estimate 95 % confidence intervals around cost differences and the uncertainty surrounding the ICERs. Uncertainty surrounding the ICERs will be graphically presented on cost-effectiveness planes. Cost- effectiveness acceptability curves [78] will also be estimated. Adjustment for confounders and effect modifiers will be done if necessary. In the budget impact analysis, the effectiveness of interventions will be extrapolated using a simple Markov model over a period of 5 years based on the estimates obtained from the proposed study. Societal, government (Budget Kader Zorg) and insurer perspectives will be considered. Different scenarios will be evaluated including: 1) the intervention is not implemented, 2) the intervention is offered to the whole patient population, 3) the intervention is implemented over a period of 4 years, and 4) the intervention is only offered to subgroups of the potential patient population. These subgroups will be defined based on the results of the study, e.g. subgroups that particularly benefit from the intervention. The total number of patients eligible for the intervention will be estimated based on Dutch incidence and prevalence rates of MDD. Resource utilization is calculated by multiplying the number of eligible patients with the resource utilization rates obtained from the economic evaluation. Different prices will be used to value resource use depending on the perspective of the analysis. Both resource use and annual costs will be presented over a 5-year period for all perspectives. Aggregated and disaggregated total costs per year will be presented for the different perspectives and scenarios. We expect that the largest economic benefits generated by the intervention will be related to reduced productivity losses. A small effect will be expected on the number of sessions needed for sustained recovery. Thus, there will be an increased capacity at mental health institutions to treat depressed patients. This will be taken into account in the BIA as well.

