### Randomization and procedure

An independent research assistant will contact eligible patients one week after the intake procedure in order to give patients additional study information and to check if the patient is motivated to participate in the study. If no structured diagnostic interview has been completed yet during the intake procedure, the research assistant will plan a diagnostic interview (SCID-I/MINI). Subsequently, if the patient wants to participate and fulfills the inclusion criteria, the patient will be invited for an online baseline assessment and to sign informed consent. After the baseline assessment, the patient will be randomized in one of the four groups by using a computer script performing block randomization (e.g. one- versus twice weekly; CBT versus IPT). Randomization (patient level) will be pre-stratified according to severity (high severity = BDI score = > 30; low severity = BDI score < =29) and treatment site. A venipuncture by experienced nurses will be planned before the start of treatment. Besides the baseline assessment, the patient will be asked to complete monthly online assessments in the course of treatment (month 1–6) and follow-up assessments at month 9, 12 and 24. This means that the moments of assessment will be equal for each group. In addition, the therapist and patient will be asked to fulfill some questionnaires during the sessions. A second venipuncture will be planned after the end of treatment (month 6).

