#### Quality of life: EQ-5D(5 L) [43, 44]

The EQ-5D consists of five health state questions (mood, symptoms of pain/discomfort, mobility, daily activities, self-care) on which respondents indicate their own health state on a scale from 0 (no problems) to 3 (severe problems) during the past week. In addition, patients will rate their overall health on a scale from 0 (worst possible health) to 100 (best possible health). The Dutch EQ-5D (5 L) tariff will be used to calculate Quality-Adjusted Life-Years (QALYs). The EQ-5D (5 L) was validated for the Dutch population [44].

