### Instruments: cost-effectiveness

#### Trimbos/iMTA questionnaire for Costs associated with Psychiatric Illness (TiC-P) – updated version 2012 [52]

Societal costs in the past three months will be measured using the TiC-P. The TiC-P consists of two different parts: part one (16 items) compromises costs due to loss of production including absenteeism from paid and unpaid work, and presenteeism. Part two (4 items) focuses on use of (psychiatric) health care including primary and secondary care, complementary care and home care. For the valuation of health care utilization standard prices [53] will be used. Medication use will be valued using prices of the Royal Dutch Society for Pharmacy [54].

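### The economic evaluation makes baseline adjustment conditional without a criterion, leaving analyst discretion and avoidable baseline noise in the QALY and cost differences

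*Protocol article*

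**What the plan says.** The section Data-analyses: cost-effectiveness relates a difference in societal costs between twice-weekly and once-weekly treatment to a difference in effects. Costs are "measured by the TiC-P at baseline and after 3, 6, 9 and 12 months". Effects are "measured with the BDI-II and quality- adjusted life-years (QALYS) based on the EQ-5D", and the horizon is "over the course of twelve months". Missing data are multiply imputed and uncertainty is bootstrapped. On covariates the section has one sentence: "Adjustment for confounders and effect modifiers will be done if necessary". It names no covariate and no criterion.

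Three other places bear on this:

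- The TiC-P looks back three months: "Societal costs in the past three months will be measured using the TiC-P" (Instruments: cost-effectiveness).
- Baseline comes before allocation: "After the baseline assessment, the patient will be randomized in one of the four groups" (Randomization and procedure).
- Allocation is stratified by BDI severity and by site (same section), not by utility or prior cost: "Randomization (patient level) will be pre-stratified according to severity".

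Table 1 reads as giving the EQ-5D and the TiC-P at 0, 3, 6, 9, 12 and 24 months. The Abstract lists cost-effectiveness and quality of life among the primary outcome measures.

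**The concern.** In a randomised comparison, a confounder is in practice a baseline variable that happens to differ between arms. An instruction to adjust only when needed is therefore naturally read as an instruction to look at the baseline table, or at the results, and then decide. Two analysts could report different ICERs from the same data and both comply with the plan. If the choice is made after seeing the data, bootstrap intervals computed under the chosen model do not reflect that choice.

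If the answer is not to adjust, precision is given away. Baseline utility is the first point of a QALY area under the curve and is likely to predict the later points. Prior cost is likely to predict later cost. Chance differences in either pass into the ICER, the cost-effectiveness plane and the acceptability curves, and then into the five-year budget impact model, which is built on the trial's estimates.

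**Working it through.** The plan gives no figure for the precision of the economic evaluation, so there is none to reproduce. Its sample-size calculation concerns the BDI-II only.

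**Inputs from the article:** EQ-5D at 0, 3, 6, 9 and 12 months within the CEA horizon; 4 × 50 patients, so 100 against 100 for the frequency comparison; TiC-P recall of three months.

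**Assumptions (not in the documents):** QALYs by the trapezoid rule; utility SD 0.15-0.25, equal at each time; carry-over c of a baseline difference to later utilities of 0.3-0.7; correlation patterns as stated below.

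**1. Weight of baseline utility.** Trapezoid weights over one year are 0.125, 0.25, 0.25, 0.25 and 0.125. Baseline has 0.125 and the later points together have 0.875.

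**2. Size of a chance imbalance.** SE of the baseline difference = SD × √(2/100).
- SD 0.15: 0.15 × 0.1414 = 0.0212
- SD 0.25: 0.25 × 0.1414 = 0.0354

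**3. Shift in QALYs for a one-SE imbalance.** Shift = SE × (0.125 + 0.875c).
- Low end: 0.0212 × (0.125 + 0.875 × 0.3) = 0.0212 × 0.3875 = 0.008
- High end: 0.0354 × (0.125 + 0.875 × 0.7) = 0.0354 × 0.7375 = 0.026
- At 1.96 SE the range is 0.016-0.051.

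**4. Precision gained by adjusting QALYs for baseline utility.** With unit variances, R² = Cov(baseline, QALY)² / Var(QALY), and the SE falls by 1 − √(1 − R²).

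With equal correlation r at all times, Cov = 0.125 + 0.875r and Var = 0.21875 + 0.78125r.

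| r | Cov | Var | R² | SE cut |
|---|---|---|---|---|
| 0.4 | 0.475 | 0.531 | 0.42 | 24% |
| 0.5 | 0.5625 | 0.609 | 0.52 | 31% |
| 0.6 | 0.650 | 0.6875 | 0.61 | 38% |

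With correlation 0.5 per three-month step, decaying with distance:
- Cov = 0.125 + 0.25(0.5 + 0.25 + 0.125) + 0.125 × 0.0625 = 0.352
- Var = 0.21875 + 2(0.1875 × 0.5 + 0.125 × 0.25 + 0.0625 × 0.125 + 0.015625 × 0.0625) = 0.486
- R² = 0.352² / 0.486 ≈ 0.25, and the SE cut is about 14%.

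**5. Precision gained by adjusting costs for baseline cost.** Assume equal SD per window and equal correlation r. The variance of the four-window total is proportional to 4 + 12r, and adjustment removes (4r)².
- r = 0.3: √((7.6 − 1.44)/7.6) = 0.90, a 10% cut
- r = 0.7: √((12.4 − 7.84)/12.4) = 0.61, a 39% cut

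**6. Cost windows against the horizon.** The four post-baseline windows cover 4 × 3 = 12 months, exactly the stated horizon. Five windows would cover 15 months, three of them before randomisation.

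**The case against.** The strongest reply is that this is a journal article. The covariate list, the form of the QALY regression and the nesting of imputation and bootstrap are commonly left to the analysis plan, and the sentence does not exclude adjustment for baseline utility or cost. This stands as far as missing detail goes, and the absence of a list is not the point here. The article does state a rule, however, and that rule is conditional without a condition.

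Second, randomisation means that chance imbalance does not bias the unadjusted estimates on average, and bootstrap intervals for an unadjusted analysis fixed in advance already include that noise. This stands in full.

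Third, every variance and correlation used above is assumed. Equal correlation favours adjustment, because it lets baseline predict month 12 as well as month 3 across a treatment phase; the decaying pattern gives a much smaller gain. Stratifying by BDI severity will also shrink chance utility imbalance to the extent that utility follows severity, so the shifts in step 3 may be somewhat high. Both points stand, and they are why ranges are given.

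A reader might also infer that pre-randomisation costs enter the ICER, because baseline is listed among the TiC-P measurements. The documents do not support that. The sentence says when the TiC-P is measured, not which forms are summed. It attributes the costs to patients in the two conditions, and before allocation no patient is in one. The twelve-month horizon fits the four post-baseline windows, and baseline costs have an ordinary use in adjustment and imputation.

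**Conclusion.** The point holds as a criticism of the conditional adjustment rule. The article allows the decision on adjustment in an evaluation of outcomes listed as primary to follow sight of the data. An unadjusted result would be less precise than the collected data permit. The consequence is discretion, conditional error and lost precision, not systematic bias.

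Under the assumptions stated, the QALY standard error would fall by roughly 14-38% with baseline adjustment, and a one-SE imbalance moves the QALY difference by about 0.008-0.026. The lower end of the first range is as defensible as the upper. The role of the baseline TiC-P is unclear wording and no more than that. The change is worth making because it costs almost nothing.

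**What to change.** Replace the conditional sentence with a fixed rule, for example:

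> QALY differences will always be adjusted for baseline EQ-5D utility and cost differences for baseline TiC-P cost, together with the stratification factors (severity and site), within each imputation and bootstrap replicate.

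Add one clarifying sentence:

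> Twelve-month costs are the sum of the 3-, 6-, 9- and 12-month TiC-P; the baseline TiC-P is used for adjustment and imputation only.

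The cost is two sentences and a regression step inside the bootstrap. All the variables are already collected, and neither the sample size nor the assessment schedule changes.

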
## Discussion

We presented a protocol for studying the session frequency of psychotherapy. Furthermore, we focused on the underlying change mechanisms in psychotherapy and try to capture physiological processes that are hypothesized to be involved during the course of depression and psychotherapy.

The finding that a higher session frequency leads to faster and more improvement of depressive symptoms might lead to adaptions in mental health care organization, where enhancing the session frequency may lead to shorter CBT and IPT treatments and will optimize the (cost) effectiveness of treatments for depression. In this case, not only patients’ suffering, but also the societal burden of depression can be reduced. The finding that a greater session frequency leads to a better and faster treatment outcome might give us insight into the mechanisms of change. Actually, if we find that a greater session frequency leads to better and faster treatment outcomes, we can directly test if specific or non-specific mechanisms of change explain the differences in outcome. Furthermore, by investigating differences in mechanisms of change between the different conditions we might enhance knowledge about the mediating role of nonspecific factors and therapy specific factors in therapy. For example, the finding that only patients who receive CBT improve on the CBT skills will support the hypothesis that learning CBT skills is a therapy-specific mechanism of change. Insight in the mechanisms of change and physiological processes underlying psychotherapy can further enable us to optimize treatments and help us understand human functioning beyond the context of therapy [8].

This study is the first to investigate the hypothesis that, while keeping total number of sessions equal, twice-weekly sessions lead to better outcomes than once-weekly sessions for depression in a head-to- head comparison. Furthermore, by including frequent assessments of hypothesized mechanisms of change, the inclusion of moderators (to specify subsets of patients who respond to specific mechanisms) and using advanced statistical techniques we hope to provide the optimal conditions for detecting mechanisms of change in psychotherapy for depression. Because patients are randomized to type of therapy this study provides the unique opportunity to compare differences between CBT and IPT with regard to session frequency and the mechanisms of change. Another strength of this study is the inclusion of physiological assessments. Over the past decades, there has been an increasing interest in a multidimensional approach for understanding the various forms of mental health disorders. It seems important to not only investigate mental disorders from self-reports or behavioral observations but also to focus on the biological aspects, including genetic and other molecular phenomena [15]. Hopefully, including physiological assessments in the study protocol will contribute to a more comprehensive understanding of depression across the course of psychotherapy.

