**Method:**

In a multicenter randomized trial, two hundred depressed patients will be recruited from Dutch specialized mental healthcare centers and randomized into one of the following groups, all receiving a maximum of 20 sessions in different frequencies: a) twice-weekly sessions at the start of CBT, b) twice-weekly sessions at the start of IPT, c) once-weekly sessions at the start of CBT, d) once-weekly sessions at the start of IPT. Primary outcome measures are depression severity, cost-effectiveness and quality of life. Process measures include therapeutic alliance, recall, therapy-specific skills, motivation and compliance. Assessments will take place during baseline, monthly during treatment and follow-up at month 9, 12 and 24. In addition, at 12 and 24 months, the frequency of depressive episodes in the previous year will be assessed. Blood samples will be taken pre- and post-treatment. The study has been ethically approved and registered.

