
### Frequency of psychotherapy

Several studies have shown an association between the frequency of therapy sessions and symptom improvement [16–18]. More specifically, a recent meta-regression found a strong and positive association between the number of sessions per week and the effect size of psychotherapy for adult depression. In that study it was session frequency, in contrast to the total number of sessions, which was related to treatment outcome [7]. In routine mental health care, therapy sessions are commonly planned once a week. The original CBT manual by Beck does recommend two sessions a week in the beginning of therapy [1]. Most empirical trials (mostly from the US) have established that CBT is efficacious providing twice-weekly treatment [19, 20]. However, Beck’s guidelines have not been followed consistently and Dutch mental health guidelines do not even give an indication of the frequency of psychotherapy for depression [6]. Given this gap between recommended and actual practice, it seems important to investigate whether a higher intensity of treatment will lead to better and more rapid treatment outcomes and is related to lower rates of relapse. The question is whether the results of the controlled clinical trials can generalize to clinical practice when an empirically-supported treatment is not implemented in the manner in which it was done. Although both conditions will have the same maximum number of sessions, it is conceivable that patients in the twice-weekly condition will respond more quickly and need fewer sessions than patients in the once-weekly condition. This could lead to a reduction of both direct (e.g. health care) and indirect costs (e.g. fewer work-days lost). In addition, differences in treatment intensity might not only lead to differences in the length of treatment, number of sessions and a reduction of costs but also to the activation of different components of therapy within different phases of the treatment. It is possible that some components of therapy will become more effective or present when patients receive sessions twice a week instead of once a week. Furthermore, it will be interesting to see whether therapy type (CBT vs IPT) moderates the effect of initial session frequency (twice-weekly versus once-weekly). This study will be the first in the field of depression that directly tests the hypothesis that twice-weekly sessions lead to better outcomes than once-weekly sessions. If we find twice-weekly sessions to be more effective or to lead to more rapid recovery, this could lead to treatment adaptations that have the potential to reduce the societal burden of depression. In addition, the question why a particular session frequency is more effective than the other might lead to new directions for understanding change mechanisms in psychotherapy.

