### Interventions

In the Netherlands, cognitive behavioral therapy (CBT) and interpersonal therapy (IPT) are the most frequently practiced evidence- based psychological interventions for depression. Both therapies are applied in weekly sessions in routine clinical settings. CBT for depression is based on the manual by Beck [1] and IPT is based on the manual by Klerman [2]. The interventions will be offered in the participating mental health centers. Participants in the experimental condition (twice-weekly sessions) will receive 16 sessions during the first 8 weeks of treatment, and 4 sessions during the last 8 weeks (up to 20 sessions during 16 weeks). Patients in the control condition (once-weekly sessions) will receive 16 sessions during the first 16 weeks and 4 sessions during the last 8 weeks (up to 20 sessions during 24 weeks). Treatment manuals are used for all interventions and both treatments will contain 12 to 20 sessions of 45 minutes, depending on the individual progress of the patients. Qualified therapists who received additional training from prof. [name] (CBT) and prof. [name] (IPT), experts in their respective modalities, will deliver the interventions. Therapists participate in only one of the therapy conditions (CT or IPT) and will consult each other on current cases in biweekly consultation meetings. The sessions will be videotaped.

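### The Discussion says the total number of sessions is kept equal, but only the 20-session maximum is; the trial compares two schedules whose length depends on progress

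*Protocol article*

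**What the plan says.** The Discussion describes the comparison as one made at a constant amount of treatment: "This study is the first to investigate the hypothesis that, while keeping total number of sessions equal, twice-weekly sessions lead to better outcomes".

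Other parts of the protocol article describe something different:

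- Abstract, Method: the four groups are "all receiving a maximum of 20 sessions in different frequencies".
- Interventions, on length: "both treatments will contain 12 to 20 sessions of 45 minutes, depending on the individual progress of the patients".
- Interventions, on the twice-weekly schedule: patients "will receive 16 sessions during the first 8 weeks of treatment, and 4 sessions during the last 8 weeks". The sentence goes on to give 20 sessions in 16 weeks as an upper limit. The once-weekly arm has the same 16 + 4 pattern over 24 weeks, also with 20 as the upper limit.
- Background, Frequency of psychotherapy: the arms share a maximum, but "it is conceivable that patients in the twice-weekly condition will respond more quickly and need fewer sessions than patients in the once-weekly condition".
- Data-analyses, cost-effectiveness: "A small effect will be expected on the number of sessions needed for sustained recovery". The text adds that the capacity this frees will enter the budget impact analysis.

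The Discussion itself also says that more frequent sessions may shorten both therapies.

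**The concern.** An equal maximum is not an equal total. If length depends on how the patient is doing, and frequency is expected to change how quickly patients improve, then the number of sessions received is a consequence of the allocated schedule. The article cannot hold that number constant and also count a difference in it as a benefit.

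This matters because equal sessions are part of the trial's rationale. The Background cites a meta-regression in which outcome was related to session frequency rather than to the total number of sessions, and presents this trial as the direct test. A reader who takes the Discussion clause literally will read any result as the effect of frequency at a fixed amount of therapy. If twice-weekly patients finished earlier with similar BDI-II scores, the finding would be the same outcome from fewer sessions. Under the clause as written it could be reported as frequency making no difference.

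**Working it through.** **1. The plan's own figure.** Sample size inputs: effect size 0.45, two-sided alpha 0.05, power 0.80. The normal approximation gives n = 2 × (1.960 + 0.842)² / 0.45² = 77.5, rounded up to 78 per arm. The two-sample t-test gives 78.5, rounded up to 79. The stated 79 reproduces. Number of sessions does not enter the formula, so this point leaves it unchanged.

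**2. What is equal and what is not.**

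| Quantity | Twice-weekly | Once-weekly | Equal by design? |
|---|---|---|---|
| Maximum sessions | 20 | 20 | Yes |
| Permitted length of a course | 12 to 20 | 12 to 20 | Range only |
| Sessions received | set by progress | set by progress | No |

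The range is 20 − 12 = 8 sessions, and 8 / 20 = 40% of the maximum. Arm means could differ by anything up to 8 sessions without breaching the protocol. That is an outer bound and not a forecast. The article calls the expected effect small and gives no figure, so a likely difference cannot be derived.

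**3. The two statements of length under Interventions.** The first phase contains 16 sessions. A 12-session course reaches its end at week 12 / 2 = 6 in the twice-weekly arm (first phase ends at week 8) and at week 12 in the once-weekly arm (first phase ends at week 16). In both arms it stops inside the first phase and never reaches the final 4 sessions. The upper-limit wording lets 16 + 4 be read as the full-length schedule, which eases the conflict. It does not say how a course shorter than 16 sessions fits a phase that patients are said to receive in full.

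**4. What each pattern of results would show.**

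| Outcome, twice-weekly vs once-weekly | Sessions received, twice-weekly vs once-weekly | Reading |
|---|---|---|
| Better | Equal or fewer | Extra sessions do not explain it; supports the frequency hypothesis |
| Better | More | Frequency and amount of treatment cannot be separated |
| Similar | Fewer | Similar outcome with less treatment, not absence of a frequency effect |
| Similar | Equal | Closest to the comparison that the Discussion describes |

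Which row applies will be known only from the sessions received. The design does not fix it in advance.

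**The case against.** The strongest reply is that this is one loose clause in a novelty sentence. The abstract, Background and Interventions all state the maximum correctly, and no analysis or sample size depends on the clause. The intention-to-treat comparison of two randomised schedules with a common cap is sound. The direction that the article expects is fewer sessions with twice-weekly treatment, so a benefit in that arm would still support the hypothesis. All of this stands. It limits the point to what may be concluded, but does not make the clause true.

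Some of the support is also softer than a quick reading suggests. The Background calls fewer sessions conceivable, not expected; the cost-effectiveness section is the firmer source. The 16 + 4 schedule carries the upper-limit qualifier and is not a rigid total.

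A fewer-sessions result would not be invisible either. Time to recovery is analysed by Cox regression, health-care use enters the economic evaluation, and kept appointments are listed in Table 2.

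A reader might infer three stronger things that the article does not support:

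- *That the trial can say nothing about frequency.* The first row of the results table shows otherwise.
- *That unequal cumulative sessions before month 6 are a flaw.* On the planned schedules they are 16 against 8 at week 8 and 20 against 16 at week 16. Two frequencies with one total must differ along the way; that is the contrast under test.
- *That the equal-sessions claim can be rescued by comparing BDI-II at a common session number.* Session 8 falls at about week 4 in one arm and week 8 in the other, so frequency would be mixed with elapsed time. Reaching session 12 is itself an event after randomisation, so the comparison would also select patients. Adjusting the main analysis for session count would likewise break the randomised comparison.

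**Conclusion.** The Discussion credits the trial with a property that it lacks. Only the 20-session maximum is equal. The number received may run from 12 to 20 by progress, and the article itself expects frequency to affect the number needed. This is more than clerical, because separating frequency from amount of therapy is the stated motivation and the clause governs how the result will be read.

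The consequence is limited. The randomised comparison of the two schedules is valid as planned. Attribution to frequency at an equal number of sessions is not secured by the design. The only sizes that the article supports are the 8-session (40%) permitted range and an unquantified small expected effect. The conclusion assumes that the 12-to-20 statement applies as written.

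**What to change.** 1. In the Discussion, replace the equal-total clause with a statement that the two arms have the same maximum number of sessions (20).
2. State the conclusion as a comparison of two schedules, each with progress-dependent length.
3. Report the number of sessions received by randomised frequency, from the appointment records already listed under Compliance and in Table 2. Read it descriptively beside the primary result, not as an adjustment.
4. Reconcile the 16 + 4 (up to 20) schedule with the 12-to-20 statement under Interventions. Which of them applies is for the trial team to state.

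The cost is a change of wording and one descriptive table from data already planned, with a slightly weaker novelty claim. The Trial status section says that recruitment is ongoing, so the correction can be made before results are known.
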